#### 2.3.2 Sample size calculation of the main trial.

Under the Null hypothesis that dapagliflozin reduces the oxalate concentration in the 24h urine by the effect shown in the exploratory phase compared to the baseline value, we will re-calculate the needed number of participants to demonstrate this effect with 90% power and a 5% alpha error in a two-sided test. In expectation of dropouts an additional number of patients of 20% of the calculated sample size will be added to the study collective.

The sample size will be calculated by using G*Power Version 3.1.9.4 with the following parameters: two-sided t-test, expected effect size 25%; significance level = 0.025; power = 0.9; alpha error 5% dropout rate 20%.

### 2.4 Trial participants

#### 2.4.1 Trial participants of the exploratory phase.

We plan to include a group of 22 persons in the exploratory phase recruited out of participants suffering from cardiomyopathy and/ or diabetes mellitus. By that, no harm must be feared and especially the diabetic and cardiomyopathy participants will have an indication and a proven benefit of dapagliflozin. Provided that the participants will not suffer any effects pharmaceutical agents that have the potential to interfere with dapagliflozin such as thiazide diuretics, alkaline bicarbonate, bisphosphonate, calcium supplementation, carbonic-anhydrase inhibitors, denosumab, glucocorticoids, loop diuretics, teriparatide, topiramate, xanthin-oxidase inhibitors or 1,25-OH-Vitamin D will be paused four weeks prior of the study to prevent data corruption by through interferences.

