#### 1.3.2 Preventive measures for recurrent kidney stones.

The current basis for the conservative treatment of recurrent kidney stones is lifestyle modifications, citrate supplementation, and pharmaceuticals. After the first episode of kidney stones lifestyle modification is recommended to every patient. Those with low-risk factors for recurrence do not require medication. Lifestyle modification alone is sufficient. High-risk patients require additional preventive measures including supplements and drug treatment adjusted to their metabolic situation [18–21,61].

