#### 2.4.2 Trial participants of the main trial.

As mentioned earlier, the exact sample size will be calculated out of the data of the interim analysis (see 2.3.2 Sample size calculation of the main trial). We plan to include two equal groups in an RCT design. Like above, pharmaceutical agents that have the potential to interfere with dapagliflozin will be paused four weeks prior to the study.

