### 2.7 Ethical concerns/ risk assessment

We plan a prospective pharmacological randomized cross-over single-center study to find out the effectiveness of dapagliflozin in high-risk patients with recurrent kidney stones. The current preventive therapies previously discussed vary widely and have low to zero success rates in many cases. [21,62,63]. The prospective collection and evaluation of blood and urine samples will determine the efficacy of dapagliflozin for this special group of patients. The performance of our study will be according to the principles of the Declaration of Helsinki 2008. The study has received approval from the Institutional Review Board of the Medical University of Vienna (1205/2022).

The planned study procedures in the current prospective observational project are all embedded in the standard of care procedures. At the study visits samples of blood and urine specimens (approx. 60 ml and 9 ml) will be collected to show if dapagliflozin therapy will produce results in this specific group of patients; that do not pose a potential harm to the study participants. However, we assume that no participant will be subjected to any potential harm related to their participation in the study. No interventional procedures will be performed if not clinically indicated. Due to the assumption that dapagliflozin will reduce the oxalate output, there is a probability that participants will experience a significant benefit from the study project. The results from this trial however have the potential of adding significant insight into the efficacy of dapagliflozin therapy in patients with a high risk of recurrent urolithiasis. These results potentially could be highly valuable for future patients in improving their quality of life, kidney function, and kidney stone-related mortality. This study was initially submitted to the EudraCT database under the identifier 2022-000994-13. However, per the regulatory transition requirements, the study has been submitted to the Clinical Trials Information System (CTIS) under the identifier 2024-519371-25-00. This ensures compliance with the latest clinical trial regulation (Regulation (EU) No 536/2014), which mandates the migration of EudraCT studies to CTIS for harmonized trial management and transparency. Both identifiers are provided for reference and traceability.

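### Existing drugs are paused for data reasons, under a proviso that concedes possible effects, while the risk assessment calls all procedures standard of care, assumes no potential harm and omits the pause

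*Protocol article*

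**What the plan says.** **Exploratory phase.** Section 2.4.1 recruits patients with cardiomyopathy and/or diabetes and states that harm is not to be feared. The next sentence begins "Provided that the participants will not suffer any effects pharmaceutical agents that have the potential to interfere with dapagliflozin". It then gives examples, "such as thiazide diuretics, alkaline bicarbonate, bisphosphonate, calcium supplementation, carbonic-anhydrase inhibitors, denosumab, glucocorticoids, loop diuretics, teriparatide" and others, and says that these agents "will be paused four weeks prior of the study to prevent data corruption by through interferences".

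**Main trial.** Section 2.4.2 refers back to the rule above and says that "pharmaceutical agents that have the potential to interfere with dapagliflozin will be paused four weeks prior to the study". It repeats neither the drug list nor the proviso.

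**Risk assessment.** Section 2.7 says that the planned procedures "are all embedded in the standard of care procedures", and section 3.2 repeats this. Section 2.7 adds that nothing interventional is done without a clinical indication, and that "we assume that no participant will be subjected to any potential harm related to their participation in the study". It discusses blood and urine sampling and the expected benefit of dapagliflozin. It does not mention the pause.

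**The concern.** The protocol gives a data reason for the pause, not a clinical one. Taking a participant off an existing drug so that the urine data are cleaner is a change of treatment made for the study. The statements that everything is standard of care, and that no potential harm is assumed, leave this change out. Loop diuretics and glucocorticoids are on the list, and the exploratory participants are recruited because they have cardiomyopathy and/or diabetes. The statement therefore bears on safety and on what section 2.7.3 promises participants about the disclosure of risks.

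There is a second, lesser issue. The exploratory phase is a single group measured before and after treatment. Its effect sizes the main trial (2.3.2 and work package 3), and its results decide whether the main trial starts (2.6.1). If it is unclear who is off which drug, and until when, the content of that estimate is also unclear.

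**Working it through.** The plan states no figure on this point, so there is none to reproduce. The check sets the passages side by side and then counts weeks.

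**1. Reason for the pause against standard of care.** Section 2.4.1 gives the prevention of corrupted data as the purpose. Sections 2.7 and 3.2 place all planned procedures within standard of care. A withdrawal made for the sake of the data does not meet that description.

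**2. Proviso against absence of harm.** The proviso makes the pause depend on participants not suffering effects. A condition of this kind is needed only if effects are possible. The sentence before it says harm is not to be feared, and 2.7 assumes there is no potential for harm. These statements do not agree.

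**3. Whether the proviso works as a rule.** The sentence is grammatically broken and names no criterion and no assessor. The exclusion list in 2.4.4 has no entry for a patient who cannot stop a listed drug. Section 2.2.2 keeps out of the main trial those with medications that predispose to stones, but does not name them. The text therefore does not settle whether a patient who cannot stop is left out, enrolled on the drug, or taken off it.

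**4. Exploratory phase against main trial.** Section 2.4.2 refers back to 2.4.1. The reference may carry over the drug list, the proviso, or both. The text does not say.

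**5. Length of the pause.** Inputs: a four-week lead-in (2.4.1 and 2.4.2), exploratory phase weeks 1–6 (work package 2), main trial weeks 7–40 (work packages 4 to 8). No end is stated.

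| Reading | Exploratory | Main trial |
|---|---|---|
| Ends at study start | 4 weeks | 4 weeks |
| Runs throughout (assumption) | 4 + 6 = 10 weeks | 4 + (40 − 7 + 1) = 4 + 34 = 38 weeks |

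**6. What the open end means for the exploratory estimate.** Baseline samples are taken before the phase begins, and response samples at weeks 4 and 6. If the pause ends at study start, listed drugs may be resumed just as dapagliflozin begins, and without a control group the two changes cannot be separated. If the pause runs throughout, this does not arise. If the proviso keeps a patient on a stable listed drug, the drug is present at both measurements and need not bias the within-patient change. The share of participants on a listed drug is not given, so no size can be attached.

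**The case against.** The strongest reply is that the contradiction is mostly one of wording. The standard-of-care sentence in 2.7 concerns study procedures and is followed directly by blood and urine sampling. The no-harm sentence is framed as an assumption. Section 2.7.2 lets a participant stop at their own or their physician's request, or for a health risk. Section 3.2 allows extra visits if clinically indicated. All of this is correct. It softens the conflict without removing it, because an assumption of no potential harm should take account of a possible effect that the protocol itself recognises, and the risk assessment is where the pause should appear.

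Four stronger readings are tempting, and the document does not support them.

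- **The main-trial rule is unconditional, so the two phases treat the same patient in opposite ways.** Section 2.4.2 refers back to 2.4.1 and may import the proviso. Nor does 2.4.1 say that a patient who cannot stop is enrolled on the drug; such a patient may equally be left out.
- **The pause contradicts the treatment the protocol says stone formers need.** Section 1.3.2 does say "High-risk patients require additional preventive measures including supplements and drug treatment adjusted to their metabolic situation". That is background, and sections 1.4.2 and 1.5 qualify it heavily: they report weak evidence and the loss of a guideline recommendation for the thiazide. The supplement described in 1.4.1 is alkaline citrate, whereas the pause list names alkaline bicarbonate. The exclusions in 2.4.4, such as hyperuricosuria and osteoporosis, may also remove likely users of some listed drugs.
- **The pause lasts 10 and 38 weeks.** These are upper readings; the text fixes only the four weeks before the study.
- **The sizing estimate is biased.** This is possible under some readings and is not demonstrated.

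**Conclusion.** The concern holds as a contradiction within the protocol. A study-driven pause of existing drugs, with a proviso that concedes possible effects, is inconsistent with the assurance on harm in 2.4.1, with the standard-of-care statement in 2.7 and 3.2, and with the assumption of no potential harm in 2.7. The risk assessment does not mention the pause. It is also unclear whether the proviso applies in the main trial, what happens to a patient who cannot stop a listed drug, and when the pause ends.

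The pause lasts between 4 and 10 weeks in the exploratory phase and between 4 and 38 weeks in the main trial. The upper figures assume that it runs to the end of each phase and that the main trial starts at week 7. No effect on the primary crossover comparison is shown. The effect on the exploratory estimate cannot be sized from the document. The point merits correction because it bears on patient safety and is cheap to put right. No view is taken on which drugs should be paused.

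**What to change.** Sections 2.4.1, 2.4.2, 2.7 and 3.2 must be reconciled.

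- The sponsor's clinicians decide and state, for each phase, whether the proviso applies, what happens to a patient who cannot stop a listed drug, and when the pause ends. The two phases need not have the same rule, but each must have a clear one.
- Section 2.4.1 drops or qualifies its assurance on harm. Sections 2.7 and 3.2 say that listed drugs may be withheld for study purposes, in place of the claim that all procedures are standard of care with no potential harm. The disclosure of risks promised in 2.7.3 should follow the corrected text.
- Use of listed drugs is recorded at the study visits. If any exploratory participant stays on one, the exploratory effect is shown with and without those participants before it is used to size the main trial.

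**Cost.** Wording changes in the protocol, one concomitant-drug field per visit and one sensitivity analysis. No extra samples are needed.

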#### 2.4.2 Trial participants of the main trial.

As mentioned earlier, the exact sample size will be calculated out of the data of the interim analysis (see 2.3.2 Sample size calculation of the main trial). We plan to include two equal groups in an RCT design. Like above, pharmaceutical agents that have the potential to interfere with dapagliflozin will be paused four weeks prior to the study.

#### 2.4.3 Inclusion criteria.

The patient informed about the study procedures as described and documented by the signed consent formAge >18 yearsCalcium-oxalate stone formers with a high risk of reoccurrence are defined as:A. At least two symptomatic or surgically treated kidney stones within the last 10 years; In particular; patients who have experienced at least two distinct symptomatic or surgically treated kidney stone episodes within the last 10 years, confirmed by imaging or surgical retrieval. Each episode must be separated by a period where the patient was either stone-free or had no symptoms, as verified by clinical evaluation or imaging to exclude the possibility of residual fragments from previous procedures, and/orB. Single stone kidney formers with risk factors include:a. Positive medical family history on kidney stone formations of at least one blood-related relative in the first degree or at least two blood-related relatives in the second degree and/ orb. The onset of kidney stone formations within the third life decade or earlier and/ orc. Metabolic syndrome and/ ord. Obesity (BMI ≥ 30 kg/m²)

#### 2.4.4 Exclusion criteria.

Age < 18 yearsSecondary causes of reoccurrence of nephrolithiasis such as:A. Active malignancyB. Active or chronic infection of the urinary tractC. Bowel diseases (chronic diarrhea, chronic pancreatitis, inflammatory bowel disease), bariatric or intestinal surgery leading to a bowel shortened length of the bowelD. Chronic kidney disease (defined as eGFR < 30 ml/min/1.73 m^2^ for more than three months)E. Cystic fibrosisF. CystinuriaG. Eating disorders (anorexia or bulimia)H. Hyperuricosuria with or without the necessity of uric-acid lowering therapy, three or more episodes of gout arthritis within the last year before inclusion into the trialI. Hypokalemia at first study-ambulance visit (defined as blood potassium level < 3 mmol/L)J. Hyponatremia at first study-ambulance visit (defined as blood sodium level < 125 mmol/L)K. Neurogenic bladderL. Obstructive uropathy or anatomical abnormalities leading to a decreased urine flow if not treated to a fully unblocked flow of urineM. OsteoporosisN. Polycystic kidney diseaseO. Primary hyperoxaluriaP. Primary hyperparathyroidismQ. SarcoidosisR. Transplanted kidneyS. Renal tubular acidosisCurrently running of prior (within three months) participation in other interventional clinical studiesNot fully understood or signed consent form, restrictions leading to inability to understand and follow the procedure as given in the protocolKnown allergy to at least one substance used in the trial

### 2.5 Hypothesis and Endpoints

#### 2.5.1 Null hypothesis of the main trial.

Dapagliflozin therapy is not associated with a reduction of oxalate excretion in 24-hour urine by at least 25% compared to the baseline value in hyperoxaluric patients with a high risk of urolithiasis reoccurrence.

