#### 2.5.2 Alternative hypothesis of the main trial.

Dapagliflozin therapy is associated with a reduction of oxalate excretion in 24-hour urine by at least 25% compared to the baseline value in hyperoxaluric patients with a high risk of urolithiasis reoccurrence.

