## 3. Statistics

### 3.1 Statistical analysis

We plan to perform statistical analysis conforming to the standard methodology. Categorized data will be presented as absolute count and relative frequencies. Continuous data will be reported as mean and standard deviation in case of normal distribution and as median and inter-quartile range (IQR) in case of a non-normal distribution. Two-sided tests are considered to be significant with a p-value <0.05.

Analyses of continuous variables will be performed using parametric and non-parametric tests (paired t-test/ Mann-Whitney-U-test). The primary endpoint is confirmatory and is the reduction of oxalate in the Verum vs. Placebophase, i.e., Dapaglifozine vs. placebo which will be compared with a two sided-t-test. Intergroup comparisons (Dapaglifozine vs placebo) will be performed by an ANOVA for a crossover design on the group of patients who went through all trial phases and corrected with Bonferroni post-hoc Tests for multiple testing. Frequencies of urolithiasis will be tested with the x²-test, a in comparison of both treatments by the McNemar-Test. Correlations between variables will be performed using Pearson or Spearman coefficients.

Findings will be corrected for multiple testing using the Tukey method if the statistical analysis is performed with a one-way ANOVA or with the Shaffer correction if the statistical analysis is performed with a Kruskal-Wallis test. All other statistical tests will be corrected using the Bonferroni-Holm method.

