#### WP9. Data evaluation and publication (post-study phase, months 16–24).

**Objective:** WP9 will comprise a thorough analysis of study results including the primary endpoint the reduction of the urine oxalate excretion by 25% under dapagliflozin therapy after 8 weeks. **Methods:** All data will be organized in a computer-based database. Statistical evaluations will be performed according to predefined models.

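### The written hypotheses set the bar at a reduction of at least 25%, but the planned t-test and its sizing address a difference from zero, so a positive result would not establish the stated alternative

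*Protocol article*

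**What the plan says.** The protocol article describes the main trial's confirmatory comparison in several places.

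- **2.5.1, null:** dapagliflozin is "not associated with a reduction of oxalate excretion in 24-hour urine by at least 25% compared to the baseline value".
- **2.5.2, alternative:** therapy "is associated with a reduction of oxalate excretion in 24-hour urine by at least 25% compared to the baseline value".
- **2.5.3, primary endpoint:** the fall in urinary oxalate after 8 weeks of dapagliflozin, against the value from the preceding washout. No percentage is given.
- **2.6 and 3.1, test:** the endpoint is called confirmatory and is "Dapaglifozine vs. placebo which will be compared with a two sided-t-test". No margin or shifted null value is given. Section 3.1 sets significance at p < 0.05.
- **2.3.2, sizing:** the listed parameters are "two-sided t-test, expected effect size 25%; significance level = 0.025; power = 0.9; alpha error 5% dropout rate 20" percent. The same section opens with a different null: "Under the Null hypothesis that dapagliflozin reduces the oxalate concentration in the 24h urine by the effect shown in the exploratory phase".
- **WP9:** the primary endpoint is "the reduction of the urine oxalate excretion by 25% under dapagliflozin therapy after 8 weeks".

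**The concern.** These statements do not describe one test. In 2.5.1 and 2.5.2, 25% is the boundary between null and alternative. In 2.3.2 it is the effect the trial expects and is powered to detect, and in 2.6 and 3.1 it plays no part. The null in 2.3.2 also runs the other way from the one in 2.5.1, because under it the drug does lower oxalate. The comparator differs too: baseline in the hypotheses, placebo in the test.

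Since the endpoint is confirmatory, the hypotheses define what a positive result means. If the written null is tested, the trial will almost surely fail when its planning assumption is exactly right. If the test against zero is run, rejection does not carry the conclusion written in 2.5.2.

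**Working it through.** **Inputs.** From 2.3.1 and Table 1: paired t-test, 90% power, correlation r = 0.1, and row means and SDs (25% row: 1.0 ± 0.2 and 1.25 ± 0.25; 15% row: 1.0 ± 0.2 and 1.15 ± 0.23). Sections 2.3.1 and 2.3.2 state both a significance level of 0.025 and an alpha error of 5%, so both levels are shown where they matter.

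**Step 1: which null Table 1 uses.**
- SD of the paired difference = √(s₁² + s₂² − 2·r·s₁·s₂).
- 25% row: √(0.0400 + 0.0625 − 0.0100) = 0.304. Standardised effect 0.25/0.304 = 0.822.
- Exact (noncentral t) sample sizes against a null difference of zero:

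| Row | Table 1 | Two-sided 0.05 | Two-sided 0.025 |
|---|---|---|---|
| 10% | 86 | 86 | 102 |
| 15% | 42 | 42 | 49 |
| 20% | 26 | 26 | 30 |
| 25% | 18 | 18 | 21 |
| 30% | 14 | 14 | 17 |

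All five rows match a test against zero at two-sided 0.05, with power 90.7% at n = 18 in the 25% row. No test against a 25% threshold could give n = 18 at a true 25%, as Step 2 shows.

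**Step 2: the written null when the planning effect is true.**
- Testing a reduction below 25% uses t = (mean difference − 0.25)/(SD/√n).
- If the true difference is 0.25, this statistic has a central t distribution. It exceeds the upper critical value with probability α/2.
- That is 2.5% at two-sided 0.05 and 1.25% at two-sided 0.025. Neither n nor the SD enters.

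**Step 3: what a significant test against zero shows.**
- Smallest significant difference = t-critical × SD/√n.
- At n = 18, two-sided 0.05: 2.110 × 0.304/√18 = 0.151, an observed reduction of about 15% on Table 1's scale.
- At two-sided 0.025: 2.458 × 0.304/√18 = 0.176.
- For the interval to exclude 25% or less, the observed difference would have to exceed 0.25 + 0.151 = 0.401 at two-sided 0.05.

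**Step 4: how often a smaller effect is significant.**
- 15% row: SD of the difference = √(0.0400 + 0.0529 − 0.0092) = 0.289. Standardised effect 0.15/0.289 = 0.518.
- Power against zero at two-sided 0.05: 55% at n = 18 and 91% at n = 42.
- At two-sided 0.025: 42% and 85%.

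**Scale.** Table 1 expresses differences relative to the smaller mean. As a proportional fall from the larger mean, the 25% row is 0.25/1.25 = 20% and the 15% row is 0.15/1.15 = 13%. The table's own 25% case therefore falls short of a 25% reduction in the sense of 2.5.2.

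**The case against.** Several points on the other side stand.

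- **The 2.5% is generic.** At the boundary of any threshold null the rejection probability is the one-sided alpha. It matters here only because the boundary is also the planning value.
- **n = 18 is the exploratory-phase size.** The main trial is to be recalculated, with 17 to 104 participants given in the abstract. Figures for n = 18 or 42 are illustrations.
- **The zero null is inferred.** No section names it. The inference rests on the absence of any margin and on the exact match in all five rows of Table 1.
- **The test and the sizing agree with each other.** The fault lies in the hypothesis wording, and the 2.3.2 null reads like a drafting slip, since its sentence goes on to power the trial to show that effect.

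A reader might go further and infer that every significant result would be announced as a reduction of at least 25%. The documents do not say so: 2.5.3, the abstract and the confirmatory test carry no 25%. Nor do they contain a success rule based on an observed reduction of 25%. A reader might also quote one true effect at which the written null would have 90% power at n = 18. That figure depends on whether the SD is held fixed or grows with the mean as in Table 1, so it is not relied on here.

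An analysis plan not shown could settle the test, but it cannot agree with both the 2.3.2 and the 2.5.1 null. The contradiction is within the protocol text.

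**Conclusion.** The point holds as an inconsistency between the written hypotheses and the planned test. The alternative in 2.5.2 is not what the test in 2.6 and 3.1 examines, and rejecting zero difference would not establish it.

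Two results do not depend on the final sample size. The written null is rejected with probability 2.5% (or 1.25%) at a true reduction of exactly 25%. And the reduction of 15% to 25% that 2.3.1 expects lies entirely at or below the boundary of the alternative.

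The gap between significance and the 25% claim is illustrated by the threshold of about 15% at n = 18, and by the 55% and 91% of trials significant under the 15% row at n = 18 and 42. These rest on Table 1's SDs, r = 0.1 and two-sided 0.05, and will change with the recalculated size. What the trial would actually report after a significant result is not stated.

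**What to change.** 1. **2.5.1 and 2.5.2:** state the null as no difference between the dapagliflozin and placebo periods in the change of 24-hour oxalate excretion from the washout baseline before each period to week 8. State the alternative as a difference. Remove the 25% threshold from both.
2. **2.5.3, 2.6 and 3.1:** describe that same comparison, so that baseline and placebo each have one defined role.
3. **2.3.2:** replace the reversed null. Keep 25% only as the planning effect.
4. **WP9:** remove the 25% from the endpoint.
5. **Reporting:** give the estimated reduction with its confidence interval. Claim at least 25% only if the interval excludes smaller reductions.

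The cost is mainly text, with no new visits or samples. It is more than a wording change in one respect: the hypotheses now compare with baseline, and the revision makes placebo the comparator with baseline entering through the change. The planned recalculation should therefore use the variability of that comparison.

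The other coherent repair, if the sponsor wants the 25% claim to be confirmatory, is to keep the threshold, test against it, and size on a true effect above it. That is expensive. With the 25% row's SD of 0.304 held fixed, a true 30% needs about 391 evaluable participants for 90% power at two-sided 0.05, and slightly more if the SD grows as in Table 1.
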